#### Intervention completion

Patients can remain in receipt of the intervention for up to 12 months. The final patient contact will include a review of progress, information about other ongoing sources of support and creation of a final summary to be sent to the GP. Upon completion of interventions, participants will be returned to the sole care of their GPs. This transition will be clearly communicated to both the participants and their GPs.

### Outcome measurement

#### Primary outcomes

In both trials, the primary outcome will be the proportion of patients who respond to treatment. In the CVD risk trial, response to treatment is defined as the maintenance or reduction of 10-year cardiovascular risk estimated on the basis of QRISK2 score [20] after 12 months. Because CVD risk increases with age, maintaining 10-year risk over 12 months requires an improvement in at least one modifiable risk factor. Throughout the study, QRISK2 score will be calculated using the same version of the QRISK2 algorithm provided as a batch processor to the research team by the authors of QRISK2. QRISK2 outcome scores will be calculated by changing age and the modifiable risk factors only. Variables such as diagnosis of diabetes or atrial fibrillation and whether the patient has been prescribed BP-lowering medications will be held constant using baseline values. This is because it is possible that the extra support provided by the intervention may result in an increased number of patients in the intervention arm receiving a diagnosis or starting medication, which in turn would inflate risk scores in this group only. In the depression trial, response is defined as a PHQ-9 score <10 and an absolute reduction in PHQ-9 ≥5 after 4 months [21,36].

#### Secondary outcomes and process measures

Secondary outcomes and process measures are listed in Table 1. These measures will be included in both trials unless otherwise indicated.

**Table 1 T1:** **Secondary outcomes and process measures **^
**a**
^

**Outcomes**	**Measures used**
Depression score (depression trial only) as a binary outcome at 8 and 12 months and as a continuous variable at 4,8 and 12 months	PHQ-9 [21]
Ten-year CVD risk score (CVD risk trial only) as a binary outcome at 6 months and as a continuous variable at 6 and 12 months	QRISK2 [19] variable obtained by clinical assessment
Quality of life	EQ-5D-5 L [37]
Patient satisfaction	Items constructed for present research and taken from Y4Q1 GP Patient Survey
Patient perceived access to care	Items adapted from TMQ [38] and items constructed for present research
Physical activity	Health-directed behaviour domain of heiQ [39]
Individual cardiovascular risk factors that is blood pressure, cholesterol, smoking status, weight, BMI (CVD risk trial only)	Clinical assessment
Diet (CVD risk trial only)	STC [40] anglicised for present use
Use of telehealth	Items constructed for present research
Internet use and experience	Items constructed for present research
Self-management skills and self-efficacy	Self-monitoring and insight, constructive attitudes and approaches, skill and technique acquisition, and healthcare services navigation domains of heiQ [39]
Medication adherence (depression trial asked only about antidepressant medication; CVD trial asked about antihypertensive and cholesterol-lowering medications)	Morisky Medication Adherence Scale [41]
Health literacy	Items adapted from eHEALS [42]
Care coordination	Subscales adapted from a measure of continuity questionnaire [43]
Anxiety (depression trial only)	GAD-7 [44]
Resource use	Items constructed for present research
Demographics	Various items taken from the Y4Q1 GP Patient Survey, 2001 census and Health Survey for England, 2007

^a^*BMI*, Body mass index; *CVD*, Cardiovascular disease; *eHEALS*, eHealth Literacy Scale; *GAD-7*, Generalized Anxiety Disorder 7-item scale; *heiQ*, Health Education Impact Questionnaire; *PHQ-9*, Patient Health Questionnaire; *STC*, Starting the Conversation; *TMQ*, Treatment Motivation Questionnaire.

### Data collection and follow-up

Data will be collected from self-report questionnaires, primary care medical records, NHS Direct Healthlines Service records and clinical measurement. Information will be collected at baseline from all participants, but the timing of follow-up data collection will differ between the two trials (as detailed below). The primary method of patient self-report data collection will be via online questionnaires. However, alternative completion methods, including on paper or by telephone, will be offered to maximise response rates. The quality of life measure (EQ-5D-5 L) will not be available for online completion, owing to licensing and technical restrictions, and thus will be completed on paper by all participants. Reminders communicated by e-mail, telephone and post will be used if participants do not return their questionnaires. The baseline questionnaire will include sociodemographic characteristics, comorbidities, current treatments, employment status and all secondary outcome measures. Follow-up questionnaires will include primary and secondary outcome measures and use of healthcare resources. Details regarding medication prescriptions and primary care contacts will be collected from primary care medical records for all participants 12 months after randomisation. For those in the intervention groups in both trials, information about the type, number and length of contacts with intervention staff will be collected from NHS Direct Healthlines Service records. In addition, anonymised information, including age, gender and ethnicity (both trials) and CVD risk score and component data (CVD risk trial only), will be obtained from practice records of invited patients who decided not to participate in the study.

In the CVD risk trial, self-report questionnaires will be completed at three time points: at baseline and 6 and 12 months after randomisation. At each of these time points, patients will also be asked to attend an appointment with a nurse at their GP practice. The nurse will collect CVD risk factor information, including a blood test to measure cholesterol (at baseline and 12 months only), BP, weight and smoking status (all time points). This information will be used to calculate the individual QRISK2 score.

In the depression trial, self-report questionnaires will be completed at four time points: at baseline and 4, 8 and 12 months after randomisation. The PHQ-9 questionnaire will be completed at each of these time points. At baseline, it will be completed as part of an initial screening questionnaire by post; at all other time points, it will be included with the follow-up questionnaire and therefore completed online or by post. Participants who do not return their follow-up questionnaires will be contacted by post and telephone to ask them to complete the PHQ-9 alone.

### Statistical considerations

#### Sample size

This study is based on analysis of data from 240 patients in each of the intervention and control groups for both the CVD risk and depression trials. The primary outcomes for both CVD and depression are binary, indicating response to the intervention. Assuming equal numbers in each trial arm for analysis and that all other parameters in a sample size estimate remain constant, the detectable between-group difference for a binary outcome is maximised when the overall proportion in the trial defined as responding is 50% (for example, 57% responding to NHS Direct Healthlines interventions and 43% responding to usual care). As the overall proportion responding increases or decreases from 50%, so the detectable difference decreases. Thus, with a sample size for analysis of 240 per arm, the absolute detectable difference between the trial arms with a 5% two-sided α and 80% power is 14 percentage points or less (1.7 equivalent odds ratio). With a 1% α and 90% power, it is 18 percentage points or less (2.1 equivalent odds ratio). For this trial, there is no accepted minimum clinically important difference. Therefore, the sample size was chosen pragmatically, taking into account the size of effect that would be likely to influence policy and practice and which might be feasible using this intervention.

Regarding the CVD risk trial, a previous study reported 38% of treated hypertensive patients 60 to 80 years of age in a control group had a reduced absolute cardiovascular risk at the 12-month follow-up examination [45]. Regarding the depression trial, response to treatment using the PHQ-9 is defined as a score <10 and a reduction of at least 5 points. In a previous trial involving a similar patient group, the response in the control group was approximately 30% [46]. If the proportion in the control arm in either of our trials is in the 30% to 38% range, 240 participants per arm for analysis will have 80% power (5% α) and 90% power (1% α) to detect differences of 13 and 18 percentage points, respectively.

Assuming 20% noncollection of primary outcome data at follow-up, it will be necessary to recruit 300 patients in each of the intervention and control groups for each trial, or 1,200 patients in total.

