#### Hours and mode of operation

The NHS Direct Healthlines Service will be available from Monday to Friday from 10 AM to 8 PM and on Saturday from 10 AM to 2 PM. The service will provide an initial assessment followed by regular telephone contacts at prearranged appointment times. Where possible, all contacts with an individual patient will be made by the same staff member in order to promote continuity of care and build rapport. The work of intervention staff will be supported by computer software, which will be used to guide the content of the telephone calls and create a record of what was discussed. In addition, patients will be able to request a call-back between their scheduled appointments via the intervention website or by leaving a telephone voice mail message.

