In addition to the regular telephone calls and support for using resources available online, the intervention incorporates several other features designed to address components of the underlying theoretical model. Because one recognised problem with previous telehealth interventions was low patient engagement, intervention-mapping was used to identify features that would act as barriers or facilitators to patient engagement. As a result, the intervention has been designed to address perceived barriers and highlight factors that would facilitate and reinforce engagement. One factor discovered during the developmental work to enhance patient engagement was the importance of support from a named person rather than from an impersonal call centre. Therefore, participants will be offered follow-up from the same HIA as much as possible. Previous telehealth interventions have also had problems related to engagement of primary care clinicians [25]. The present research aims to address this problem by framing the intervention as supportive and working with primary care clinicians rather than duplicating their efforts or competing with them. Accordingly, letters are regularly sent to the GPs about each patient’s progress during the course of the intervention. Letters making recommendations about treatment are also accessible to patients, which reinforces patient engagement and may make it more likely that recommendations will be acted upon.

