#### Primary analysis

By using intention-to-treat analyses, we will compare groups using logistic regression models adjusted for baseline values of the outcome and stratification/minimisation variables, paying attention to 95% confidence intervals as well as *P*-values. Sensitivity analyses will be conducted using standard techniques to impute missing data.

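### The power statement and the stated primary model make no allowance for clustering by health information advisor, which may arise in the intervention arm only

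*Protocol article*

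**What the plan says.** **Delivery.** Patients are randomised individually. Only the intervention arm is treated by advisors, who work as a team in an NHS Direct call centre. Under Hours and mode of operation, the aim is that "all contacts with an individual patient will be made by the same staff member in order to promote continuity of care and build rapport"; the sentence opens with the qualifier that this applies where possible. The Intervention content section repeats the aim: "participants will be offered follow-up from the same HIA as much as possible". It gives as the reason that developmental work found support from a named person important for engagement. The calls are described as the core of the intervention: 12 over a year in the CVD risk trial, and seven plus two in the depression trial.

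**Sample size.** "This study is based on analysis of data from 240 patients in each of the intervention and control groups". The general statement is that the detectable difference at "5% two-sided α and 80% power is 14 percentage points or less (1.7 equivalent odds ratio"). For the expected control rates ("If the proportion in the control arm in either of our trials is in the 30% to 38% range") the section says that "240 participants per arm for analysis will have 80% power (5% α) and 90% power (1% α) to detect differences" of 13 points (80% power, 5% α) and 18 points (90% power, 1% α). The only inflation is for 20% missing primary outcomes, giving 300 per arm.

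**Primary analysis.** The groups are compared by "logistic regression models adjusted for baseline values of the outcome and stratification/minimisation variables". The stratification and minimisation variables are location, practice and baseline score. A full statistical analysis plan is promised before any analysis, but it is not available here.

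**The concern.** If advisors differ in how well they help patients, those who share an advisor have correlated outcomes. That adds variance to the intervention arm mean. The two-proportion formula leaves this variance out, and a logistic model without an advisor term does not estimate it. Practice is in the model, but the advisors sit in a call centre and nothing in the article ties them to practices, so adjusting for practice should not be expected to absorb advisor variation.

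The protocol itself treats the advisor relationship as something that matters, so an ICC of exactly zero is not a safe default. At stake are the credibility of a borderline positive result in a study meant to inform policy, and the reading of a null result against a power figure that may be too favourable.

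**Working it through.** **Inputs from the article:** 240 analysed per arm; control response 30% to 38%; difference 13 points; two-sided α 5%.

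**Inputs assumed, because the article gives neither:** 6, 12 or 20 advisors per trial, with equal caseloads m = 240/advisors, and an ICC of 0.01, 0.02 or 0.05.

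**Step 1: reproduce the stated figures with independent patients.** Let p̄ be the mean of p0 and p1.
- SE0 = √[2·p̄(1−p̄)/240]
- SE1 = √[(p0(1−p0) + p1(1−p1))/240]
- Power = Φ[(d − 1.96·SE0)/SE1]

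For 38% v 51%: SE0 = 0.0454, SE1 = 0.0450, power = Φ(0.91) = 82%. For 30% v 43%: SE0 = 0.0439, SE1 = 0.0435, power = Φ(1.01) = 84%.

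The difference detectable with 80% power is 12.3 points (30% control), 12.7 points (38% control) and 12.8 points (centred on 50%). At 1% α and 90% power the corresponding figures are 17.1, 17.5 and 17.5. And 240/0.8 = 300. So the stated 13, 14 and 18 points are independent-patient results rounded up. The only slack is that rounding, worth 2 to 4 percentage points of power at 13 points.

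**Step 2: add advisor clustering to the intervention arm only.**
- Design effect DE = 1 + (m−1)·ICC
- SE1 = √[(p0(1−p0) + DE·p1(1−p1))/240]
- SE0 = √[p̄(1−p̄)(1+DE)/240]
- Ratio of correct to unadjusted SE ≈ √[(1+DE)/2]
- Type I error of an unadjusted 5% test ≈ 2·[1 − Φ(1.96/√((1+DE)/2))]

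Example with 10 advisors and ICC 0.02: m = 24 and DE = 1 + 23 × 0.02 = 1.46. For 38% v 51%, SE0 = 0.0503, SE1 = 0.0500 and power = Φ(0.63) = 73%. The SE ratio is √1.23 = 1.11 and the type I error is 7.7%.

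| Advisors (m) | ICC | DE | Power for 13 points, 30% / 38% control | Detectable difference at 80% power, 30% / 38% control (points) | Unadjusted type I error |
|---|---|---|---|---|---|
| 20 (12) | 0.01 | 1.11 | 82% / 80% | 12.6 / 13.0 | 5.6% |
| 20 (12) | 0.02 | 1.22 | 80% / 78% | 12.9 / 13.4 | 6.3% |
| 20 (12) | 0.05 | 1.55 | 75% / 72% | 13.9 / 14.3 | 8.3% |
| 12 (20) | 0.01 | 1.19 | 81% / 78% | 12.9 / 13.3 | 6.1% |
| 12 (20) | 0.02 | 1.38 | 77% / 75% | 13.4 / 13.8 | 7.2% |
| 12 (20) | 0.05 | 1.95 | 68% / 66% | 15.0 / 15.4 | 10.7% |
| 6 (40) | 0.01 | 1.39 | 77% / 75% | 13.5 / 13.9 | 7.3% |
| 6 (40) | 0.02 | 1.78 | 71% / 68% | 14.6 / 15.0 | 9.6% |
| 6 (40) | 0.05 | 2.95 | 56% / 53% | 17.5 / 17.9 | 16.3% |

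Using the unpooled variance in place of SE0 moves these powers by less than one percentage point; the most favourable cell becomes 83% / 80%.

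**Step 3: find where the slack runs out.** Power for 13 points reaches 80% at DE = 1.10 (38% control) or 1.24 (30% control). From ICC = (DE−1)/(m−1), that is 0.005 or 0.012 with 12 advisors, 0.003 or 0.006 with 6, and 0.009 or 0.021 with 20.

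**The case against.** Four points on the other side have force.

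- **Continuity is an aim, not a rule.** Both statements are qualified. A reader might infer that every patient has exactly one advisor by design, but the text does not say so. Changes of advisor and low engagement would weaken the clustering, though they would not remove it.
- **Advisor differences may be small.** Common three-week training, call review, software-guided scripts, online CBT, automated blood pressure advice and treatment review by the GP all limit the scope for variation. With 20 advisors and ICC 0.01, power is still 80% to 82%. With 10 advisors and ICC 0.02, the difference detectable around a 50% response is 14.0 to 14.1 points depending on the variance formula, which is essentially the general figure of 14 already stated.
- **The analysis plan is not shown.** It may add a random effect or a robust variance. It therefore cannot be said that the final analysis will ignore advisors, only that the model as worded does. The power statement is different: it is made in this article without qualification.
- **Type I inflation is conditional.** It needs advisors who truly differ around an average effect of zero. If the intervention changes nobody's outcome, advisors add no variance and the unadjusted test keeps its size.

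All four stand as limits on the size of the problem. None alters its direction when the ICC is positive, and none supplies an allowance that the stated calculation lacks.

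**Conclusion.** The point holds in conditional form. The stated power and the stated primary model treat all patients as independent, although the delivery plan makes correlation within advisor plausible in one arm. For any positive ICC, power is lower than calculated and unadjusted intervals are too narrow.

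Over 6 to 20 advisors per trial and ICC 0.01 to 0.05 (both ranges assumed), power for 13 points runs from about 82% or 83% down to 53%. The correct standard error is 1.03 to 1.41 times the unadjusted one. If advisors vary around a zero mean effect, the type I error is about 5.6% to 16%. At a 38% control rate the rounding slack is gone at a design effect of about 1.1.

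A reader might infer that the trials are underpowered or that 80% power is not reached. The document does not support that: it gives neither the number of advisors nor an ICC, and in the mild cases the stated power is met. The calculation also assumes equal caseloads, full continuity and a normal reference distribution.

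**What to change.** 1. Obtain each intervention patient's advisor identifier along with the contact type, number and length already to be drawn from the Healthlines Service records. Identity is not among the items listed, so it has to be requested. Set in advance how patients with more than one advisor are assigned.
2. Prespecify for the primary outcome a partially nested logistic model, with a random advisor effect in the intervention arm only and controls as singletons. Make it at least a named sensitivity analysis. That is the safer place for it if advisors are few.
3. Report the estimated ICC and the number of advisors in each trial.
4. Qualify the 13-point detectable difference with a range for advisor clustering, stating the number of advisors and the ICC values used.

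Enrol no more patients; randomisation is reported as complete. The cost is one extra identifier, a few lines in the analysis plan, a somewhat less favourable power statement, and possible instability of the model when there are few advisors.

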#### Descriptive analysis

The analysis and presentation of each trial will be carried out in accordance with Consolidated Standards of Reporting Trials guidelines. Appropriate descriptive statistics will be used to compare characteristics of invited patients who did or did not agree to take part and eligible patients who were randomized or not randomized. We will also examine the balance of patient characteristics at baseline across the trial groups.

#### Primary analysis

By using intention-to-treat analyses, we will compare groups using logistic regression models adjusted for baseline values of the outcome and stratification/minimisation variables, paying attention to 95% confidence intervals as well as *P*-values. Sensitivity analyses will be conducted using standard techniques to impute missing data.

#### Secondary and subgroup analyses

Analysis of secondary outcomes, the effect of adherence to the intervention and preplanned subgroup analyses for the primary outcome will be conducted using appropriate multivariable regression models. The subgroups of interest are age, sex and baseline CVD risk or PHQ-9 score. Subgroups broken down by the type of modifiable risk factor at baseline (for example, high BP, obesity, smoker) will be analysed in the CVD risk trial only. Additional subgroups of interest may also be identified by the process evaluation. Analysis of additional subgroups will be agreed upon with the Data Monitoring Committee and the Trial Steering Committee, and all analyses performed will be reported. A full statistical analysis plan will be developed and agreed upon with the Trial Management Group, the Data Monitoring Commitee and the Trial Steering Committee prior to any analyses.

#### Protection against bias

Allocation will be concealed by use of a remote automated system. Blinding of participants, HCPs and researchers is not possible. We recognise that patients in the control group may be able to access similar information from other websites, including NHS Choices, although we think that such usage will be much less than in the intervention group because the latter will be directed to these resources by NHS Direct Healthlines Services staff. We will collect patient self-report information about the use of other relevant web-based resources by all participants.

### Research governance

Management, operational and academic aspects of the trials are the responsibility of the Trial Management Group, which meets approximately every 6 weeks. Conduct of the trials will also be overseen by an Independent Trial Steering Committee and an Independent Data Monitoring Committee. The whole research programme is also overseen by the Healthlines Programme Management Group, which includes all the coapplicants on the programme grant and patient and public representatives. The University of Bristol is the study sponsor, and the study has been approved by the National Research Ethics Service Committee South West–Frenchay (Reference 12/SW/0009).

### Economic evaluation

The aim of the economic evaluation will be to estimate the costs and benefits of the NHS Direct Healthlines intervention in managing patients with raised CVD risk or with depression and to assess the cost-effectiveness of the telehealth packages in these contexts. There will be two stages of this evaluation: (1) patient-level evaluations covering the period of the trial and (2) modelling of future costs and benefits to cover the lifetime of the trial population. The patient-level evaluations will be carried out prospectively alongside the depression and CVD risk trials. These evaluations will take into account the perspectives of the healthcare provider (NHS) and personal social services (PSS), patients and lost productivity due to time taken off from work.

